#### General management

Maintenance of anaesthesia as well as haemodynamic management during and after cardiopulmonary bypass are standardised and protocol-driven according to the hospital’s SOPs. All patients are sedated and ventilated during transfer to the ICU. A blood gas analysis is performed before the start of the study intervention and 1 h after study infusion termination. Blood gas analyses are performed every 2 h for the next 6 h and thereafter according to clinical routine. Additionally, renal ultrasonography is performed to assess renal blood flow prior to infusion as well as at 1 h and 2 h after termination of the study fluid and on the first postoperative day.

#### Fluid management and haemodynamic protocol in the ICU

On admission to the ICU, patients will receive 5 ml/kg ideal body weight of HS (7.3% NaCl) or NS (0.9% NaCl) by infusion pump for 60 min. Thereafter, ICU treatment will continue according to clinical routine.

If needed, norepinephrine is the first-choice vasopressor and will be titrated to a mean arterial pressure (MAP) judged adequate for the respective patient depending on age and history of hypertension and kidney injury. The range of target MAP is typically between 55 and 65 mmHg. Epinephrine will be added when an additional agent is needed to maintain adequate blood pressure, and if necessary norepinephrine will be exchanged for epinephrine. Dopamine is not used. In the presence of myocardial dysfunction — as suggested by increased cardiac filling pressures and low cardiac output — a dobutamine infusion will be administered. If patients become hypertensive, afterload will be reduced by nitroprusside natrium infusion.

#### Management of biological material

Two samples of blood as well as a urine sample will be drawn and stored at − 80 °C at the four defined time points (Fig. 1). Coded samples will be stored by the Center of Laboratory Medicine, Inselspital, Bern University Hospital, Switzerland.

### Safety measures during study conduct

The infusion of HS can lead to several side effects including electrolyte disturbances (hypernatraemia, hyperchloraemia, hypokalaemia), occurrence of acidosis, and development of oedema. Hence the following safety measures are taken: Before the start of the study intervention, in the ICU a secondary screening will be performed. First, a blood gas analysis will be done before the start of the study intervention to ensure a serum sodium concentration postoperatively below 145 mmol/L and a serum chloride concentration below 107 mmol/L. Second, a doctor of the research team will be contacted if intraoperative complications such as massive bleeding, severe haemodynamic turbulence, or intraoperative myocardial infraction occurred. Based on the blood gas analysis results and/or the medical history, it will be decided if the study is to proceed. Patients admitted from the ICU with cardiac assist devices such as an IABP or an ECMO device or electrolyte levels outside the normal range will be dropped from the study before receiving the study intervention.

If the study is started, a blood gas analysis will be performed 1 h after study infusion termination. For the first 20 patients we will perform a blood gas analysis after 30 min and 60 min of study infusion to check serum sodium levels; thereafter, if the sodium levels stay below 155 mmol/L during infusion of the study fluid, this additional blood gas analysis will be omitted. One hour after termination of the study infusion an additional blood gas analysis will be performed; thereafter, blood gas analyses will be performed every 2 h for the next 6 h and thereafter according to clinical routine.

If the serum sodium level is above 155 mmol/L or the serum chloride level is above 125 mmol/L at any time point, the infusion of the study medication will be stopped.

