### Randomisation and blinding

All patients undergoing cardiac surgery and meeting the eligibility criteria as defined above will be enrolled in the study and randomised to either the HS group (7.3% NaCl) or the NS group (0.9% NaCl). Computerised randomisation using a variable block size [2, 4, 6] will be performed by a member of the study team not involved in any part of treatment (neither nurse, resident, nor supervisor). A box with the study vials and study infusion will be given to the treating intensive care physician with the patient’s number in the study. Participants, care providers, investigators, and outcome assessors will be blinded to study group assignment. A list for emergency un-blinding of the study will be held by a designated study quality manager.

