### Study conduct

Patients included in the trial will receive standard monitoring for cardiac surgical patients in the ICU. We routinely monitor oxygen saturation, heart rate, invasive arterial blood pressure, electrocardiography, temperature, urine output, and central venous pressure.

Echocardiography will be performed preoperatively and intraoperatively. If patients are considered haemodynamically unstable, they receive a pulmonary artery catheter (PAC) according to the hospital’s standard operating procedures (SOPs). Blood gas analysis parameters and mixed venous oxygen saturation will be measured according to clinical routine or as indicated at the discretion of the attending ICU physician.

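### The rule that ends the in-infusion blood gases tests sodium only, although the infusion's stop rule names both sodium and chloride

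*Protocol article*

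**What the plan says.** All the rules concerned are in the protocol article, mostly under Safety measures during study conduct.

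- **Entry check.** Before the infusion a blood gas must show "a serum sodium concentration postoperatively below 145 mmol/L and a serum chloride concentration below 107 mmol/L".
- **Run-in.** "For the first 20 patients we will perform a blood gas analysis after 30 min and 60 min of study infusion"; the stated purpose is to check sodium, and no arm is named.
- **Release.** "thereafter, if the sodium levels stay below 155 mmol/L during infusion of the study fluid, this additional blood gas analysis will be omitted". Chloride is not mentioned.
- **Stop rule.** "If the serum sodium level is above 155 mmol/L or the serum chloride level is above 125 mmol/L at any time point", the infusion is stopped.
- **Listed harms.** Hypernatraemia and hyperchloraemia are both named as possible effects of HS.

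The dose, under Fluid management and haemodynamic protocol in the ICU, is "5 ml/kg ideal body weight of HS (7.3% NaCl) or NS (0.9% NaCl) by infusion pump for 60 min". Under General management, "A blood gas analysis is performed before the start of the study intervention and 1 h after study infusion termination"; further gases follow every 2 hours for 6 hours. Under Study conduct, blood gases are otherwise taken "according to clinical routine or as indicated at the discretion of the attending ICU physician".

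**The concern.** A rule that relaxes monitoring should test the same limits that the monitoring enforces. Here the stop rule has two limits and the release rule has one. If chloride exceeded 125 mmol/L in a run-in patient while sodium stayed below 155, that patient's infusion would be stopped, yet the condition for dropping the gases in all later patients would still be met.

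A second matter bears on how much comfort a clean run-in gives. The 20 patients come from both arms, and those on 0.9% saline practically cannot reach the sodium limit, so the evidence comes from the HS recipients alone.

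At stake is whether later HS patients lose the two in-infusion gases on an incomplete test. Sample size and primary analysis are not affected.

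**Working it through.** **The plan's own figures.** The article gives no calculation for the run-in of 20. Its one computed figure, 48 per group, is unrelated to this point and reproduces: 2 × (1.960 + 0.842)² × 1734² / 1000² = 47.2, rounded up to 48.

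**1. The two rules compared.** There are four possible run-in results.

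| Run-in result | Stop rule acts on that patient | Gases dropped afterwards |
|---|---|---|
| Neither limit crossed | no | yes |
| Sodium above 155 only | yes | no |
| Both crossed | yes | no |
| Chloride above 125 only | yes | **yes** |

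The last row is the inconsistency. It follows from the text and needs no assumption.

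**2. Can chloride be the nearer limit?** This needs body-water values that the article does not give. Assumed: total body water (TBW) 0.45–0.60 L and extracellular water (ECW) 0.18–0.25 L per dosed kg, complete mixing, no excretion, chloride confined to ECW with osmotic water shift.

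- HS dose: 73/58.44 × 5 = 6.25 mmol/kg in 0.005 L/kg.
- Sodium after a fraction f of the dose: (C0 × TBW + f × 6.25) / (TBW + f × 0.005).
- Chloride after the full dose: osm0 = 2 × Na0 + 10; osm1 = (osm0 × TBW + 12.49) / (TBW + 0.005); ECW1 = (osm0 × ECW + 12.49) / osm1; Cl = (Cl0 × ECW + 6.25) / ECW1. At half dose, 12.49, 6.25 and 0.005 are halved.

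*Start at sodium 144, chloride 106 (just inside the entry limits).* Sodium reaches 153.1–156.1 at full dose and 148.6–150.1 at half dose. Chloride reaches 119.0–123.4 and 112.7–115.0. For TBW 0.45 and ECW 0.18: osm1 = (134.1 + 12.49)/0.455 = 322.2; ECW1 = (53.64 + 12.49)/322.2 = 0.2053; Cl = (19.08 + 6.25)/0.2053 = 123.4. From this start sodium is the tighter limit: in that case 155 is reached at 0.90 of the dose, about minute 54, and 125 only at 1.10.

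*Start at sodium 138, chloride 106, same TBW and ECW.* Sodium = (62.1 + 6.25)/0.455 = 150.2, which is 4.8 below its limit. For chloride, osm1 = (128.7 + 12.49)/0.455 = 310.3; ECW1 = (51.48 + 12.49)/310.3 = 0.2062; Cl = about 122.8 (unrounded inputs), which is 2.2 below its limit. Over a grid of TBW 0.45, 0.50, 0.60 and ECW 0.18, 0.20, 0.25, the chloride limit would be reached at a smaller multiple of the dose than the sodium limit in all nine combinations from sodium 138, and in eight of nine from sodium 140.

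So which limit is nearer depends on the starting sodium. No combination takes chloride past 125 at full dose.

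**3. What 20 patients contain.** Allocation is 1:1 in random blocks of 2, 4 and 6. Simulated lists give 10 HS recipients among the first 20 in 81%, and 9 or 11 in about 9–10% each, if patients are treated in randomised order. The other arm receives 9/58.44 × 5 = 0.77 mmol/kg, which moves sodium from 144 to about 144.1. After no crossing in n HS recipients, the one-sided 95% upper limit on the crossing rate is 1 − 0.05^(1/n): 28% for 9, 26% for 10, 24% for 11, and 14% for 20. Release would then apply to 48 − 11 = 37 up to 48 − 9 = 39 HS patients.

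**The case against.** The strongest reply is that the gases to be dropped could hardly trigger the stop rule. The 60-minute sample falls at the end of the infusion and cannot stop it. The 30-minute sample is modelled at no more than 150.1 for sodium and 115.0 for chloride from the highest permitted start. This stands, and it is why the point is minor.

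A second reply is that sodium is the tighter limit, so testing sodium alone is enough. That holds from a starting sodium of 144, but not from 138, where chloride is nearer its limit throughout the grid.

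A reader might go further and infer that the run-in is too small and must contain 20 HS recipients. The document does not support that as a requirement. It claims no confidence limit for this check, the measured values say more than a count of crossings, and 20 HS recipients would be just as arbitrary, leaving an upper limit of 14%. A reader might also infer that release disables the stop rule. No scheduled gas then falls within the infusion, but routine and clinician-requested gases remain. Nor does the model predict that chloride will cross 125.

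The full protocol may say who judges the release and on what values. The article nevertheless states the release condition outright, and that condition names only sodium.

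**Conclusion.** The point holds as an inconsistency between two rules in one section: the gases could be released after a chloride crossing that the stop rule treats as reason to stop. This rests on the text alone. The modelled chloride margin at full dose from the entry limits, 1.6 to 6.0 mmol/L, rests on the assumed body water, complete mixing and no excretion; with ideal-weight dosing, overweight patients have more water per dosed kg and end lower.

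The upper limit of about 26% after no crossing in 10 HS recipients is something for the sponsor to recognise when relying on the run-in. It is not an error in the plan. Severity is minor: exposure would hardly change, every patient is screened on both ions beforehand, and gases resume 1 hour after the infusion.

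**What to change.** Reword the release: omit the 30- and 60-minute gases only if sodium was not above 155 mmol/L and chloride not above 125 mmol/L in all run-in patients; otherwise keep them for later patients. This also aligns the wording at exactly 155, which the present release and stop rules treat differently.

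No extra run-in sample is needed, since the pre-infusion gas already reports both ions. The only cost arises if chloride crosses: the gases then continue, at most 2 × 76 = 152 for the 96 − 20 = 76 remaining patients.

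Extending the run-in to 20 HS recipients is optional. Release would move to about patient 37–42, so 17–22 more patients with two gases each (34–44 gases). If a crossing appeared only among HS recipients 11 to 20, all 152 would be needed; at assumed crossing rates of 5% and 10% the chance of that is 0.599 − 0.358 = 24% and 0.349 − 0.122 = 23%. It would also require an arm-specific count by the holder of the unblinding list and show clinicians more sodium values that hint at the arm, in a double-blind trial whose primary endpoint is the fluid they give.

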### Study parameters

We will obtain baseline data (age, gender, height, weight, BMI), baseline comorbidities, risk scores, and preoperative and postoperative routine laboratory parameters in all patients. Additionally we will perform sonographic assessment of renal blood flow and assess body composition (bioimpedance) at predefined endpoints.

All types of fluids and the cumulative amounts (blood products included), daily body weight, and cumulative doses of medication will be documented. Furthermore, the need for renal replacement therapy, length of mechanical ventilation, length of ICU and hospital stays, and mortality will be assessed.

### Outcome measures

#### Primary endpoint

The primary endpoint is the difference in total cumulative fluid volume administered during ICU stay between patients receiving HS and patients receiving NS following elective cardiac surgery.

#### Secondary endpoints

Secondary endpoints are to investigate whether use of HS results in:Reduced cumulative vasopressor dose and shorter time on vasopressors after cardiac surgery- Differences in urinary output and postoperative weight gains between the two groups.

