**Methods:**

In a prospective double-blind randomised controlled clinical trial, we aim to recruit 96 patients undergoing elective cardiac surgery for ischaemic and/or valvular heart disease. After postoperative admission to the intensive care unit (ICU), patients will be randomly assigned to receive 5 ml/kg ideal body weight HS (7.3% NaCl) or normal saline (NS, 0.9% NaCl) infused within 60 min. Blood and urine samples will be collected preoperatively and postoperatively up to day 6 to assess changes in renal, cardiac, inflammatory, acid-base, and electrolyte parameters. Additionally, we will perform renal ultrasonography studies to assess renal blood flow before, during, and after infusion, and we will measure total body water using preoperative and postoperative body composition analysis (bioimpedance). Patients will be followed up for 90 days.

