### End of study

For included patients, the study will start with admission to the ICU and will end after day 6. Thereafter, patients will be followed up for secondary endpoints. Patients will not be monitored further if they are readmitted to the ICU.

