#### Estimation of sample size

Sample size calculation was based upon fluid data from the Hemacetat study (NCT02895659) [28], conducted at our institution with the same patient collective. Preliminary data showed that patients received a mean of 3381 ml fluid during their ICU stay, with a standard deviation of 1734 ml. A clinically relevant effect size was determined to be a reduction of 1000 ml fluid (30%).

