#### Rationale for effect size

Although several studies reported reduced infusion volumes when HS was used for fluid resuscitation [29], there is a large heterogeneity in studies on HS use, with widely varying amounts of sodium administered. In consequence, it was not possible to determine the amount of fluid to be saved when HS is used based on the available literature. Fluid overload is harmful in patients undergoing cardiac surgery and related to adverse outcomes [30–32] and thus should be avoided. However, the ideal amount of fluid for these patients is not yet clarified. In a pragmatic approach, we hence determined that it would be clinically beneficial if the total amount of fluid administered intravenously in the ICU (average 3381 ml at our institution) could be lowered by 1 L or 30%.

Modelling based on values of this study was achieved with the Power and Sample Size Calculator provided by the Statistical Institute of the Medical University of Vienna (http://statistics.msi.meduniwien.ac.at) and cross-checked on http://powerandsamplesize.com. The following constellations were obtained with regard to the required case numbers: n = 48 with a power of 80% and an α error of 0.05. Based on these results, a number of *n* = 48 patients with an IMP for each group, for a total number of 96 patients with an IMP, was determined to be sufficient.

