## Discussion

Patients undergoing cardiac surgery typically receive a significant amount of intravenous fluids to support circulatory function and counteract the side effects of rewarming after cardiopulmonary bypass [10]. In cardiac surgery patients, the influence of crystalloid solutes on the acid-base status, intracellular and extracellular water content, and plasma electrolyte composition has a substantial impact on organ function and outcome [33–35]. Additionally, changes in vascular permeability and oncotic pressure contribute to fluid leakage [36]. Therefore, these patients typically suffer from various degrees of fluid overload after prolonged ICU stay [10]. Fluid overload has previously been associated with increased mortality and morbidity in various subgroups of critically ill patients [37–39].

Preliminary data from a study conducted recently in our institution showed that fluid balance on the first postoperative day is around plus 6500 ml [40]. Therefore, the exploration of alternative fluid resuscitation strategies for patients after cardiac surgery in order to minimise fluid overload seems of paramount importance.

Previous data suggest that HS might be a safe alternative for fluid resuscitation in patients for whom fluid overload should be avoided [27]. However, data on the use of HS for this indication are scarce: Only five studies have assessed volume status as a primary target criterion after infusion of HS [22, 27, 41–43], with only one study being performed in patients after cardiac surgery [27]. The latter was a randomised controlled double-blind trial involving 72 post-cardiac surgical patients [27]. Endpoints of this study were postoperative weight gain as well as total volume balance when fluid resuscitation with 0.9% saline was compared to a bolus of 4 ml/kg 7.5% saline plus 0.9% saline [27]. The study showed a promising 10% reduction in total volume need, a 50% increase in 1-h urine production, and a 50% reduction of perioperative weight gain [27]. Nonetheless, the results of this study have not been confirmed so far.

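### Body water is measured from a preoperative value and the reference for weight gain is not stated, so these outcomes may carry variance from before the infusion that the plan adjusts for only contingently

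*Protocol article*

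**What the plan says.** The secondary endpoints include "Differences in urinary output and postoperative weight gains between the two groups". Under Study parameters, weight appears among the baseline data and is then recorded daily, but the text does not say which weight is the reference for a gain. The timing of assessments is left to Fig. 1, which is not reproduced in the copy reviewed.

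For body water, the abstract's Methods paragraph is explicit: "we will measure total body water using preoperative and postoperative body composition analysis (bioimpedance". This outcome is exploratory.

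Treatment begins after surgery. The fluid management section places the infusion at ICU admission, and End of study says that "the study will start with admission to the ICU and will end after day 6".

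Two institutional figures bear on when fluid accumulates. The Discussion reports that "fluid balance on the first postoperative day is around plus 6500 ml". The sample-size section reports that "patients received a mean of 3381 ml fluid during their ICU stay".

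Under Statistical methods, interval outcomes are compared by t test or Mann-Whitney test. Regression adjustment is added only if the groups turn out to differ at baseline. No trigger is given, and fluid balance before the infusion is not named as a covariate.

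**The concern.** Less postoperative weight gain stands beside less infused fluid in the stated hypothesis, so the outcome matters even though it is secondary. If gain is counted from a preoperative weight, as body water is from a preoperative reading, the measured change covers surgery and bypass as well as the treated period. Fluid gained before the infusion differs between patients for reasons that allocation cannot have caused. That variation enters the treatment contrast as noise. With 48 patients per arm it can blur a real effect or produce a chance difference. Adjusting only when imbalance is noticed does not recover the lost precision in the usual case, where the arms look similar.

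**Working it through.** **1. The plan's own figure.** Inputs from the sample-size sections: ICU fluid with mean 3381 ml and SD 1734 ml in the centre's earlier data; a target reduction of 1000 ml (1000/3381 = 29.6%, given as 30%); and "n = 48 with a power of 80% and an α error of 0.05".

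n per group = 2 × (1.960 + 0.842)² × 1734² / 1000² = 47.2, rounded up to 48. The stated 48 reproduces (two-sided, normal approximation). Power at 48 = Φ(1000 / (1734 × √(2/48)) − 1.960) = Φ(0.865) = 81%.

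**2. How much of the early gain precedes the infusion.** The 3381 ml is gross intake over the whole ICU stay, so it is a generous ceiling on what the ICU can have added to the balance by the first postoperative day.

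- Zero ICU output: 6500 − 3381 = 3119 ml; 3119/6500 = 48%.
- ICU output of 1000 ml (assumed): 6500 − 2381 = 4119 ml; 63%.
- ICU output of 2000 ml (assumed): 6500 − 1381 = 5119 ml; 79%.

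The two volumes come from different in-house studies, one a net balance and the other an intake, so the split is approximate.

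**3. What this does to the comparison.** These are shares of a mean. Under randomisation the expected pre-infusion gain is the same in both arms and cancels from the difference. Only its between-patient spread costs anything, and the article gives no SD for it.

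**4. Illustration of the cost.** Assume that a between-group difference of 1000 ml (about 1 kg) is of interest, that gain within the ICU has the primary endpoint's SD of 1734 ml, and that pre-ICU gain is independent of it with SD s. Then total SD = √(1734² + s²), and power at 48 per group is Φ(1000 / (total SD × √(2/48)) − 1.960).

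| Assumed s (ml) | Total SD (ml) | Power at 48 per group | n per group for 80% |
|---|---|---|---|
| 0 (ICU-admission reference) | 1734 | 81% | 48 |
| 500 | 1805 | 78% | 52 |
| 1000 | 2002 | 69% | 63 |
| 1500 | 2293 | 57% | 83 |
| 2000 | 2647 | 46% | 110 |

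Independence matters too. With a correlation of −0.3 between pre-ICU gain and ICU gain, power is 84% at s = 500 and 60% at s = 2000. With +0.3 it is 71% and 37%.

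**5. Does the existing adjustment cover this?** No. It depends on an observed imbalance and does not name the variable concerned.

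**The case against.** The strongest reply is that the weight reference is not actually preoperative on the page. A reader might infer that it is, from the listing of weight with the baseline data and from the earlier cardiac-surgery trial, which the Discussion describes in terms of perioperative gain. The text does not say so, the study is defined as starting at ICU admission, and the schedule figure may contain a pre-infusion reading. This stands: for weight, the sound statement is that the text gives no reference.

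A reader might also infer that the pre-infusion gain swamps any effect of hypertonic saline. The documents do not support that. A common offset cancels, no SD is given, and at s = 500 ml the illustrative loss is three percentage points. The Discussion also reports that the earlier trial, with 72 patients, halved perioperative weight gain. Any claim that removing the pre-ICU component would be worth a doubling of the sample rests on an assumed share of the variance.

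The additive model can also be challenged. Hypertonic saline is meant to draw fluid from the extravascular space and increase urine output, so earlier fluid is partly what it acts on and need not persist unchanged into later weights. This is a fair limit on the table. It does not count against regression, which estimates how far earlier balance carries through instead of assuming that it does so in full.

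Finally, total gain from the preoperative state has clinical meaning, since the Background defines overload as a percentage increase in body weight. An admission bed-scale weight with lines and drains in place may be noisier. That is why exchanging the reference for a new measurement is a trade-off and not a clear gain.

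What survives is that a preoperative reference is stated for body water and possible for weight, and that an unconditional adjustment is better than a contingent one.

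**Conclusion.** The point holds as a matter of precision, not of bias. Body water is referenced to a preoperative reading, and the reference for weight gain is not given in the text. Roughly half or more of the early fluid gain probably precedes the infusion, if two figures from different in-house studies may be set together. Any outcome measured from a preoperative value therefore carries variance that arose before treatment.

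The size of the loss cannot be derived from the article. On the borrowed 1000 ml and SD 1734 ml, with independence assumed, it runs from negligible (81% to 78%) to substantial (81% to 46%) as the assumed pre-ICU SD goes from 500 to 2000 ml. The outcomes affected are one secondary and one exploratory. The primary endpoint counts only fluid given in the ICU, so neither it nor the sample size of 96 is touched. This is a cheap improvement to the analysis and does not threaten the trial's validity.

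**What to change.** State the reference value and time points for weight gain. For weight-gain and body-water outcomes measured from a preoperative value, replace the contingent adjustment with a prespecified ANCOVA or linear regression that always includes treatment, the preoperative value, and the charted fluid balance up to the start of the study infusion.

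If the schedule already contains a weight or bioimpedance reading at ICU admission before the infusion, use it as the baseline covariate and report change from admission beside change from the preoperative value. A new reading is not needed for this fix.

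The cost is one extra variable taken from the operative record and slightly more analysis. The charted balance will not capture every pre-infusion change in weight, so the adjustment should recover part of the lost precision, not necessarily all of it.
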